
As empirical assumptions for the interplay between depression and loneliness in the inpatient and follow-up depression therapy are rare, we decided to set a change of 2 points in the MADRS per 1 SD of loneliness (3-Item UCLA Loneliness Scale) as the minimum meaningful association that shall be detected via the interaction (baseline x change) over the inpatient and post-treatment course. The model tested baseline loneliness and change in loneliness with at least 1.75 points MADRS as we have no empirical assumptions about which association is more significant for this setting, but we have a theoretical assumption that these single associations are less significant than their interaction. An omnibus likelihood ratio test will evaluate these assumptions in a single model, followed by Holm-Bonferroni corrected single tests to evaluate these three assumptions. This step will also evaluate the direction of effects and theoretical plausibility (more loneliness at baseline and less change in loneliness shall predict higher depressive symptom severity). The primary analysis of the linear mixed model includes all three measurement points as a categorial factor. Potential time- effects will serve as covariates in this model and will be reported exploratory with no influence on sample size calculation. Studies examining the clinical course of inpatient depression treatment measured with the MADRS report partly comparable values of MADRS at baseline (≈ 30 points) (62–64) and discharge, though findings remain heterogeneous (65, 66). Model assumptions for this sample size calculation were therefore based on plausible clinical values: T0 = 30, T1 = 16, T2 = 15 MADRS points, with a constant standard deviation of *SD* = 8 across all time points. Between-person differences in depression symptom severity (MADRS) were considered with fixed and random slopes, and ICC was set at .50. Power simulation involved assumptions of approximately 5% missing completely at random (MCAR) and 10% missing at random dropout at T2 (MAR). Sample size estimation was performed with R using the following packages: lme4, lmerTest, MASS and tidyr. The simulation for the overall model yielded a statistical power of ≥ 80% for all three assumptions at *n* = 172 with 15% combined dropout rate (MCAR, MAR), resulting in a total of *n* = 199. The number of simulations was 500 (nsim = 500) at a significance level of *α* = 0.05 for the omnibus likelihood-ratio test, with Holm-Bonferroni corrected single hypothesis tests. As depression can lead to cognitive distortion, correlations between loneliness and depression might be dependent on the measurement point, and given the insufficient clinical validation of the loneliness measures, it remains unclear whether the assumptions of a normal distribution and the assumed level of measurement adequately describe the interplay between depression and loneliness. Additional statistical methods are employed in an explorative and descriptive manner (generalized linear mixed-effects model and mixed analysis of variance). Power-analysis for mixed ANOVA using G*Power Version 3.1.9.7, with categorical groups of ‘high’ and ‘low’ loneliness (median-split) when considering an α error of 0.05, a power of 0.9 (1-β error probability) and a correlation value among repeated measures of 0.5 for the group’s results an estimated sample size of *n* = 36 participants assuming a medium effect size (*f* = 0.25), and *n* = 214 participants assuming a small effect size (*f* = 0.10).

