### Statistical analysis

2.6

To perform the statistical analysis, IBM SPSS Statistics Version 29 (96) and R (97) are used. To address the primary objective of this study, which is to examine the clinical relevance of the interplay between loneliness and depression in an inpatient and post-inpatient treatment setting, a set of statistical approaches is employed. To address the primary hypothesis, a linear mixed model with likelihood ratio test will be conducted to test against the null hypothesis that baseline loneliness, change in loneliness or their interaction have no additional association with the symptom severity in the course of depression (T0, T1, T2). In the primary linear mixed-effects model, depressive symptom severity (MADRS) is modeled across the three main assessment points (T0 = admission, T1 = discharge, T2 = three-month follow-up), with time entered as a categorical factor. Baseline loneliness at T0 (applied to T0, T1, and T2), the change in loneliness from admission to discharge (applied to T1 and T2), and their interaction (baseline × change) are entered as fixed effects, alongside random intercepts and random slopes capturing individual differences in symptom level and course. Because the length of inpatient stay differs between participants, the individual inpatient treatment duration (days from admission to discharge) is included as a time-related covariate rather than assuming a fixed interval between T0 and T1. The biweekly interim assessments are not part of the primary model and are reserved for the exploratory within-/between-person trajectory analyses described below. The primary test is an omnibus likelihood-ratio test of the null hypothesis that baseline loneliness, change in loneliness, and their interaction jointly show no association with the course of depressive symptom severity; only if this omnibus test is significant are the three individual coefficients examined, with Holm–Bonferroni correction. The formal model specification and the complete list of covariates are provided in the **Supplementary Material** (Section 4 and **Supplementary Table S1**). All models will be controlled for time-effects (e.g., length of inpatient treatment duration), measures obtained at the same timepoint (e.g. explorative analysis of measurement specific associations of loneliness and depression), recruitment site, gender and age and will be tested for further covariates such as social anxiety and social support. The primary analysis sample will include all participants who completed T0 and T1 depression severity measures (MADRS) and loneliness measures (3-Item UCLA). For each questionnaire, missing individual data points are imputed using person-mean imputation, provided that no more than 20% of the data is missing. Participants with an inpatient stay shorter than seven days (post-enrollment exclusion criterion) are not part of the primary analysis set, since no discharge assessment (T1) is obtained for them; where baseline (T0) data are available, they are retained in the sensitivity analyses of all available data. The extent and pattern of missing values will be described for all inference statistical analysis. Given that dropout is likely associated not only with observed characteristics (MAR) but also with unobserved post-discharge symptom severity (MNAR), sensitivity analyses will include pattern-mixture models or selection models to evaluate the robustness of primary findings under MNAR assumptions. As a pragmatic benchmark, a worst-case analysis will be performed assuming that all dropouts at T2 experienced no improvement (last observation carried forward) or deterioration (fixed offset of +5 MADRS points).

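### Minor, cost-free improvement: after a significant omnibus test, Holm's first step at 0.0167 tests the same joint null again; 0.025, 0.025, 0.05 would suffice

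*Protocol article*

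**What the plan says.** The Statistical analysis section (2.6) of the protocol article sets out two stages. First: "The primary test is an omnibus likelihood-ratio test of the null hypothesis that baseline loneliness, change in loneliness, and their interaction jointly show no association". Then: "only if this omnibus test is significant are the three individual coefficients examined, with Holm–Bonferroni correction".

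The Sample size consideration section (2.3) gives the same order: "An omnibus likelihood ratio test will evaluate these assumptions in a single model, followed by Holm-Bonferroni corrected single tests to evaluate these three assumptions". The power simulation is described under that rule, "at a significance level of *α* = 0.05 for the omnibus likelihood-ratio test, with Holm-Bonferroni corrected single hypothesis tests". The two sections agree. Neither says that the first Holm step is relaxed once the joint null has been rejected, so ordinary Holm on three tests applies: 0.0167, 0.025 and 0.05 for the smallest, middle and largest p-value.

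**The concern.** Holm is built to stand alone. Its first step, smallest p-value against 0.05/3, protects against a false claim when all three coefficients are zero. Here a three-degree-of-freedom likelihood-ratio test at 0.05 already gives that protection before any coefficient is examined. The same null is therefore tested twice, and the second test can only remove rejections.

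The single tests say whether admission loneliness, its change or their interaction carries the association. The redundant step makes it somewhat more likely that the omnibus test is significant and no coefficient is named. Effects below those planned are a realistic case: section 2.3 says that effect sizes in a clinical population are unknown and that the planning values were set without empirical data.

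**Working it through.** **Inputs from section 2.3.** Interaction: "a change of 2 points in the MADRS per 1 SD of loneliness". Main terms: "baseline loneliness and change in loneliness with at least 1.75 points MADRS". Spread: "with a constant standard deviation of *SD* = 8 across all time points". ICC 0.50, n = 172, total 199, α = 0.05. From section 2.6: baseline loneliness acts at T0, T1 and T2; change acts at T1 and T2.

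**Assumptions, because the article does not give these.** Two-sided single tests; standardised predictors; interaction acting at T1 and T2; random slope as a person-specific shift from T0 to the later visits, with added variance 0, 16 or 32; baseline–change correlation 0 or −0.5. Large-sample generalised least squares, 400,000 draws per scenario.

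**The plan's own figures.** 172 × 1.05 × 1.10 = 198.7, which gives 199. Power per coefficient under the planned rule at n = 172 is 0.91–0.999 with slope variance 0, 0.87–0.98 with 16 and 0.76–0.94 with 32. The statement that the simulation "yielded a statistical power of ≥ 80% for all three assumptions" is therefore compatible with moderate slope variance. It cannot be reproduced exactly without that variance.

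**Closed testing.** A coefficient may be declared non-zero if every joint null containing it is rejected at 0.05.
- All three zero: rejected by the likelihood-ratio test.
- Each pair zero: Bonferroni, smaller p ≤ 0.05/2 = 0.025.
- Each single coefficient zero: p ≤ 0.05.

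With ordered p-values p(1) ≤ p(2) ≤ p(3), the largest pair condition on p(1) is 0.025. For p(2) it is also 0.025, from the pair {2,3}. For p(3), once the first two have passed, only 0.05 remains. The sequence after a significant omnibus test is thus 0.025, 0.025, 0.05. It differs from the plan only at the first step and rejects whenever the plan does.

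**Illustration.** Take p-values 0.020, 0.060 and 0.30 with uncorrelated estimates: |z| = 2.326, 1.881, 1.036. The omnibus statistic is 5.41 + 3.54 + 1.07 = 10.02, above the critical value 7.81. The plan names nothing, since 0.020 > 0.0167. The closed rule names the first coefficient.

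**Family-wise error.** Global null: about 3.3–3.5% under the plan, 3.9–4.1% under the closed rule. With some effects non-zero and at least one true null, neither rule exceeded 5%.

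**Gain at the planned effects.** 0 to 0.3 points per coefficient.

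**Gain with one non-zero coefficient at its planned size.** Examples: 0.775 to 0.785 and 0.753 to 0.769. The range is about 0.5 to 2 points, and less where power is already very high.

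**Gain at half the planned effects (0.875, 0.875, 1.0), all coefficients positive:**

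| Slope variance | Correlation | At least one named: plan → closed | Omnibus significant, none named: plan → closed |
|---|---|---|---|
| 0 | 0 | 73.2% → 78.5% | 11.7% → 6.5% |
| 0 | −0.5 | 76.2% → 80.4% | 8.1% → 3.9% |
| 16 | 0 | 58.7% → 64.6% | 14.0% → 8.0% |
| 16 | −0.5 | 58.1% → 63.1% | 10.0% → 5.0% |
| 32 | 0 | 47.6% → 53.2% | 13.1% → 7.5% |
| 32 | −0.5 | 48.4% → 53.3% | 10.4% → 5.4% |

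If the change coefficient has the opposite sign and the correlation is −0.5, the gain in naming at least one reaches nearly 7 points (62.6% → 69.4% with slope variance 16). Per coefficient, the half-effect gains are about 1 to 3 points.

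**The case against.** The strongest reply is that nothing here is wrong. An omnibus test followed by Holm is standard, pre-specified, consistent across both sections and controls family-wise error. Its cost is already in the power simulation, which is described under the same rule. The larger gains arise only below the effects the plan calls its minimum meaningful association, and naming at least one coefficient is the most favourable measure. All of this stands, and it is why the point is minor.

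Holm also controls family-wise error whatever the size of the likelihood-ratio test, whereas the closed rule needs that test to hold 5% under the joint null. Section 2.3 itself doubts normality and the level of measurement. This is a fair caveat, though the omnibus test is the primary test and its level has to be trusted in any case.

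Two stronger readings are tempting and not supported:
- A reader might infer a noticeable saving in participants, because the first critical value falls from |z| = 2.39 to 2.24. The omnibus test stays in place under both rules. A lone |z| of 2.24 contributes only 2.24² = 5.0 towards the required 7.81, so for a lone effect the omnibus test usually binds first.
- A reader might infer that a significant omnibus result with no named coefficient is uninterpretable. The plan makes the omnibus test the primary test, and the Discussion counts the hypothesis as confirmed if any of the three terms is associated. Such a result answers the primary question; it only leaves open which term is responsible. The closed rule makes it rarer but does not remove it.

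**Conclusion.** The planned procedure is valid and needlessly conservative at one step. This is an inefficiency, not an error, and neither the sample size nor the power statement is undermined. The redundancy, and the 5% bound for the closed rule, follow from closed testing without simulation, given a likelihood-ratio test that holds its level. The sizes of the gains rest on the assumed slope variances (0–32), correlations (0 to −0.5) and a large-sample approximation. They are negligible at the planned effects and small for a lone effect. They are modest at half the planned effects, where the chance of a significant omnibus test with no coefficient named falls by roughly a third to a half.

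**What to change.** In sections 2.3 and 2.6, keep the omnibus likelihood-ratio test at 0.05 as the first stage. Then state that, if it is significant, the ordered p-values of the three coefficients are compared with 0.025, 0.025 and 0.05, stopping at the first failure, and that family-wise error is held at 5% by closed testing. The cost is one sentence in each place. No new data or larger sample is needed, and no rejection under the present rule is lost. The wording should be fixed before outcome data are examined. If the sponsor prefers ordinary Holm because it does not depend on the level of the likelihood-ratio test, a sentence giving that reason would also settle the matter.

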The primary hypothesis states that loneliness (3-Item UCLA Loneliness Scale) at admission, the change in loneliness from admission to discharge, and their interaction (admission x change in loneliness) will significantly predict depressive symptom severity, assessed using the Montgomery–Åsberg Depression Rating Scale (MADRS), in a linear mixed-effects model, tested using an omnibus likelihood ratio test (*α* = .05). As depression is our main outcome variable, we will also address this hypothesis for self-report data, measured with the Patient Health Questionnaire (PHQ-9). The loneliness scores of the 6-Item De Jong Gierveld Loneliness Scale will serve for sensitivity analysis to examine the measurement robustness and construct validity. A more detailed but exploratory analysis of the fixed and random effects and time-varying loneliness and depression within the inpatient and follow-up treatment period will be explored with linear mixed model analysis to 1) examine whether loneliness has a role in the inpatient therapy effect on depression symptom severity and its maintenance after discharge, 2) investigate the clinical relevance of chronic loneliness, and 3) describe the bidirectional relationship between loneliness and depression at all measures. To evaluate the prognostic value of baseline loneliness (3-Item UCLA Loneliness Scale) to predict response at discharge (≥ 50% reduction in MADRS) and the prognostic utility of loneliness at discharge to predict relapse (≥ 10 MADRS points more from discharge to follow-up or ≥ 22 MADRS points at follow-up), receiver operating characteristics (ROC) will be determined and reported in an exploratory fashion. Along with the main objective to investigate the clinical relevance of loneliness and depression, we will test several exploratory hypotheses. Since the duration of inpatient treatment has implications for the allocation of healthcare resources, we will test whether loneliness at admission and change in loneliness from admission to discharge are significant predictors of inpatient length of stay after adjusting for covariates. The secondary objective of the study is to identify the biopsychosocial processes that shape the interaction between loneliness and clinical depression. To this end, statistical analyses of additional clinically relevant outcomes (such as quality of life and suicidality) as well as interactional effects of potentially shared psychosocial mechanisms (including social support, social network, comorbidities, general health and physical activity) will be conducted. Exploratory analysis of blood, saliva and stool markers including metabolic, hormonal, immunological, and neurotrophic factors as well as microbiome diversity will deepen the understanding of pathophysiological processes. We hypothesize that more depressed and more lonely people will have the most unfavorable metabolic profile in blood markers (Low-Density-Lipoprotein, HbA1c), higher levels of inflammation or cellular stress (sphingolipid metabolism) and less neuroplasticity (BDNF). In terms of saliva pattern markers, we assume a higher stress response (cortisol, α-amylase activity) in individuals with more severe depression and loneliness. For stool markers, it is hypothesized that more depressed and lonely people have a less diverse stool microbiome (alpha-diversity). We hypothesize the changes in biomarker profile from baseline to discharge from clinic and baseline to follow-up to be associated with changes in depression severity and changes in loneliness experience.

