### Inclusion and exclusion criteria

2.2

To be included in this study, individuals must meet the following inclusion criteria: (A) inpatient elective or emergency admission to one of the two psychiatric clinics; (B) age over 18 years; (C) sufficient understanding of spoken and written German; (D) primary diagnosis of depression according to ICD-10 (F32 or F33), as diagnosed by a physician or clinical psychologist in conjunction with the M.I.N.I. Screen [Mini-International Neuropsychiatric Interview Screen (57)] and M.I.N.I. [Mini-International Neuropsychiatric Interview (58–60)] diagnostic tools; and (E) informed voluntary consent. Diagnoses are coded according to the International Classification of Diseases (ICD-10-GM) applicable in Germany, both for psychiatric disorders and for non-psychiatric comorbidities. The M.I.N.I., a structured clinical interview, is based on both the Diagnostic and Statistical Manual of Mental Disorders (DSM-V) and the ICD-10-GM. This additional instrument is intended to supplement the diagnostic process, increase diagnostic certainty, and better characterize suicidality and psychiatric comorbidities, with our focus particularly on anxiety disorders. The following exclusion criteria were applied: (a) a current lack of capacity to provide consent (e.g., pronounced psychotic symptoms, stuporous depressive syndrome, and thought constriction to suicidality); (b) previous participation in the study; (c) pregnancy or breastfeeding; and (d) an inpatient stay of less than 7 days, even if the patients initially met the inclusion criteria (post-enrollment exclusion).

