##### Inpatient treatment duration

2.4.2.7

The number of days from the beginning of inpatient treatment to the day of discharge from inpatient therapy will be recorded.

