
Sensitivity analysis will be performed including all available participant data (including T0 only post-enrollment exclusion analysis and analysis of cases with missing data at T0/T1), and further covariates and confounding variables. Additional covariates as medication, comorbidities, social network size and therapy participation, among others, are recorded and classified in a structured manner, for example, medication based on substance classes and treatment strategy (monotherapy/augmented therapy and changes in dosing or substances). Loneliness is being exploratory evaluated in terms of its significance and clinical relevance as a potential predictor of the course and change in severity of depression. For a more differentiated analysis, within-person and between-person variation will additionally be distinguished in an exploratory manner — both for depressive symptom severity and its individual change, and for loneliness and its individual change. The biweekly interim assessments of loneliness and depression are incorporated into this exploratory, hypothesis-generating part of the analysis, which is oriented toward potential intervention targets. It should be noted that, at the interim time points, loneliness is available from the 3-Item UCLA Loneliness Scale, whereas depressive symptom severity is available by self-report only. Accordingly, the PHQ-9 is administered at the biweekly assessments — and likewise at T0, T1, and T2 — to capture self-reported depressive symptom severity.

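### Criterion (d) excludes enrolled patients on length of stay, a listed outcome, and the T0-only sensitivity analysis cannot test what this does to the change and interaction terms

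*Protocol article*

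**What the plan says.** Section 2.2 lists as exclusion (d) "an inpatient stay of less than 7 days, even if the patients initially met the inclusion criteria (post-enrollment exclusion"). Table 1 gives the inpatient phase a minimum of 7 days.

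Section 2.4.2.7, under secondary outcomes, defines inpatient treatment duration: "The number of days from the beginning of inpatient treatment to the day of discharge from inpatient therapy will be recorded". The Introduction adds an exploratory test of whether "loneliness at admission and change in loneliness from admission to discharge are significant predictors of inpatient length of stay after adjusting for covariates", and motivates it by the allocation of healthcare resources.

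Section 2.6 gives the consequence for the main analysis: "Participants with an inpatient stay shorter than seven days (post-enrollment exclusion criterion) are not part of the primary analysis set". The same sentence then explains why, and says what remains of these patients' data: "since no discharge assessment (T1) is obtained for them; where baseline (T0) data are available, they are retained in the sensitivity analyses". Further on, the section describes these sensitivity analyses as "including T0 only post-enrollment exclusion analysis and analysis of cases with missing data at T0/T1".

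In the primary model the terms enter on different rows: "Baseline loneliness at T0 (applied to T0, T1, and T2"), but "the change in loneliness from admission to discharge (applied to T1 and T2").

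The MNAR analyses in section 2.6 are motivated by post-discharge symptom severity, and the worst-case benchmark covers dropouts at T2.

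**The concern.** There are two linked problems.

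**Length of stay.** Criterion (d) is worded as an exclusion from the study, and it acts on the value of an outcome that the study wants to explain. Patients leave within a week for reasons that may relate to loneliness, such as early discontinuation or quick improvement. Dropping them selects on the dependent variable. For the change predictor this cannot be avoided, because no T1 exists. For admission loneliness it is needless wherever T0 was done: the predictor is measured and the discharge date is in routine data. A question about use of inpatient days loses its shortest stays.

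**The sensitivity analysis.** The primary test concerns baseline loneliness (β1), change (β2) and their interaction (β3). A patient with T0 only has no change score and no row on which β2 or β3 acts. A sensitivity result that agrees with the primary one could be taken as reassurance about all three coefficients, although two of them were hardly exposed to the check.

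**Working it through.** **Plan figures.** The article gives no share of stays under 7 days and no expected distribution of stay, so there is no plan figure to reproduce here. The power simulation in section 2.3 assumes about 5% MCAR and 10% MAR dropout at T2 and does not mention short-stay exclusion. The total of 199 is close to the usual inflations of 172 (172/0.85 = 202.4; 172 × 1.15 = 197.8) and is used below only as an n.

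**A. Truncation, single distribution.** Assume log stay is normal and correlates r = 0.2 with loneliness. Let p be the share below 7 days, c = Φ⁻¹(p), λ = φ(c)/(1 − p) and v = 1 + cλ − λ². The slope in the retained patients divided by the slope in all is v / (1 − r²(1 − v)).

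| p | c | λ | v | ratio |
|---|---|---|---|---|
| 2% | −2.054 | 0.049 | 0.896 | 0.90 |
| 5% | −1.645 | 0.109 | 0.810 | 0.82 |
| 10% | −1.282 | 0.195 | 0.712 | 0.72 |
| 20% | −0.842 | 0.350 | 0.583 | 0.59 |

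Simulation agrees (0.90, 0.81–0.82, 0.71–0.72, 0.60). On the scale of days the ratios run from about 0.95–0.96 at 2% to 0.76–0.82 at 20%. If the median and spread are assumed instead (median 28 to 56 days, log-SD 0.5 to 0.9), c = ln(7/median)/log-SD. The share under 7 days is then 6% or less, and the ratio lies between 0.79 and 1.00.

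**B. Truncation, separate early leavers.** Assume early leaving follows a logistic model in loneliness, and other stays are log-normal with median 42 days, log-SD 0.5 and a shift of 0.075 per SD of loneliness. Linear slopes in days per SD:

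| early leavers | odds ratio per SD | all enrolled | stay ≥ 7 days |
|---|---|---|---|
| about 5% | 1.0 | 3.4 | 3.6 |
| about 2% | 1.5 | 3.1 | 3.6 |
| about 5% | 1.5 | 2.5 | 3.6 |
| about 11% | 1.5 | 1.5 | 3.6 |
| about 12% | 2.0 | about 0 | 3.5–3.6 |

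Model A shrinks the slope and model B enlarges it, so the retained data alone cannot give the sign of the bias.

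**C. What T0-only rows can show.** Inputs from section 2.3: MADRS means 30/16/15, SD 8, ICC 0.50, effects 1.75 (β1), 1.75 (β2) and 2 (β3). The random-slope variance is not in the text, so a random intercept only was used, with n = 2,000 per replicate and baseline and change independent. 10% are excluded.

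| selection depends on | coefficient | short stayers excluded | T0 rows added | full data |
|---|---|---|---|---|
| T0 values | β1 | 2.13 | 1.78 | 1.78 |
| T1 state | β2 | 1.55 | 1.55 | 1.76 |
| T1 state | β3 | 1.77 | 1.77 | 1.99 |

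Adding T0 rows leaves the standard errors of β2 and β3 unchanged (ratio 1.000). At 20% excluded with selection on T1 state, β2 is 1.47, 1.47 and 1.76, and β3 is 1.66, 1.66 and 1.98. At n = 199 with 10% excluded, adding the rows moves β2 and β3 by 0.005 and 0.008 on average, against standard errors of 0.43 and 0.44.

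Independence of baseline and change is not essential. With a correlation of −0.5 and selection on T1 state, β2 goes from 1.60 to 1.57 against 1.76 in full data, so it does not approach the full-data value. With selection on T0 values it goes from 1.86 to 1.77 (full data 1.78), a correction that comes through β1.

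**The case against.** **Truncation is not stated.** The sentence in section 2.6 concerns the primary analysis set, which belongs to the MADRS model. The length-of-stay analysis is exploratory, has no analysis set of its own in the article, and a condensed article may leave that to a fuller document. This stands in part: a reader might infer that the plan expressly drops short stays from this analysis, and it does not say so. But section 2.2 excludes these patients from the study, and section 2.6 brings them back only in sensitivity analyses with T0 data. Truncation is therefore the result of following the text.

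**The sensitivity analysis is not empty.** A reader might conclude that it is uninformative, or the only check. The documents do not support that. Baseline loneliness acts on T0 rows, so selection on baseline values can be seen and corrected, as part C shows. Excluded and retained patients can be compared at T0, and section 2.6 also promises a description of the extent and pattern of missing values.

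**T0 may be missing too.** One might assume that every short stayer has a T0. Table 1 lets T0 fall from day 0 to day 7, and section 2.6 keeps these patients only where baseline data exist. Some selection on stay would remain after any fix.

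**A minimum stay has a rationale.** The MADRS covers the preceding seven days (section 2.4.1.1.1), so the admission and discharge ratings of a short stayer could overlap, and the Discussion describes treatment lasting several weeks. This supports the rule for the T0–T1 change analysis. It gives no reason to drop short stays when stay itself is the outcome.

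**The size is assumed.** In the 5% case of model B the shift is 3.6 − 2.5 = 1.1 days. Stays have an SD of about 25.7 days, so at n = 199 the slope has a standard error of about 25.7/√199 = 1.8 days, and the shift is about 0.6 standard errors. This is fair and limits the weight of the point.

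**Conclusion.** The point holds in two limited parts.

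First, criterion (d) excludes enrolled patients on the value of a listed secondary outcome, and nothing exempts the exploratory length-of-stay analysis. Read as written, that analysis is truncated at 7 days. The loneliness slope can be attenuated (about 10% to 40% on the log scale for an assumed 2% to 20% excluded, and 0% to about 21% over the assumed medians and spreads) or inflated (about 2.5 to 3.6 days per SD with about 5% early leavers and an odds ratio of 1.5). If short stays are rare and unrelated to loneliness, the effect is small (3.4 against 3.6). The share, the odds ratios and the correlation are all assumptions.

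Second, the T0-only sensitivity analysis can check selection on baseline values, but not whether selection on discharge state alters the change and interaction coefficients. This follows from the rows on which those terms act. Only its size depends on the assumed selection.

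It does not follow that the primary result is biased by a known amount. The documents do not give the share of short stayers or the reasons for leaving early.

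**What to change.** 1. Limit criterion (d) to the analyses that need T1. Run the length-of-stay analysis for admission loneliness on all enrolled patients with T0 loneliness, including stays under 7 days, using the recorded discharge date. Give the analysis restricted to stays of at least 7 days as a sensitivity analysis. Report the number of short stayers, how many lack T0, and the T0 profile of the rest.
2. State that the T0-only sensitivity analysis does not test the change and interaction terms, and extend the planned pattern-mixture or selection-model analysis to missing T1.

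Inviting short stayers to the interim forms and to T2 would not by itself cure the second problem: T2 is set at three months after T1, and without T1 there is no admission-to-discharge change score.

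The cost is changed wording in sections 2.2 and 2.6 and a little extra analysis, with no new visits. Some selection remains because T0 may be missing for the shortest stays.
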